**Fig. 1 Fig1:**
[figure not shown]
Trial flow diagram

### Study population

Community residents in greater Melbourne will be recruited to participate. Inclusion criteria are all of the following: (1) age ≥18 years (only adults will be included in the study because children required different measures for outcomes assessment) and (2) loss of control eating (defined as at least one episode of loss of control eating in the past month as assessed using the Eating Loss of Control Scale) [33]. Our definition for loss of control eating is based on previous studies which have used a similar cut-off point for their inclusion criteria [34–37]. The exclusion criteria include (1) cognitive impairment which will hinder ability to provide informed consent or to complete the questionnaires, (2) pregnant or lactating or planning to become pregnant during the study, (3) use of any medication containing NAC or other contraindicated medications within 4 weeks prior to enrolment (such as carbamazepine, nitroglycerin, anticoagulants, and antioxidant agents or glutathione prodrugs that can enhance the effect of NAC, e.g., selenium or vitamin E), (4) previous hypersensitivity to NAC, (5) known or suspected active systemic medical disorder or any serious medical illness that NAC may adversely affect (e.g., epilepsy, recent gastrointestinal bleeding, esophageal varices, renal stones, hepatic or renal failure, and asthma), (6) surgery within the past 28 days, and (7) currently using or will be using a formal weight loss program during the study.

### Sample size estimation

Sample size calculation was based on progression criterion for a pilot study as recommended by Consolidated Standards of Reporting Trials CONSORT [38]. Retention rate, defined as the percentage of individuals who complete the retrospective questionnaires at week 12, was used for sample size calculation. A total sample of 36 participants are required assuming at least 80% of enrolled participants are retained in the study compared to a worst-case retention rate of 60% or less in a one sample *t*-test with 80% power at *p* <0.05 based on the exact binomial test. The cut-off points of 60% and 80% set as the “stop” and “go” criteria provides sufficient sample size and power for the assessment of the primary feasibility outcome with the lowest expected denominator (e.g., retention rate).

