
This study will investigate the use of NAC for the treatment of loss of control eating in adults by examining the response to a dose of 2400 mg/day for 12 weeks. A recent systematic review on clinical trials of NAC found that at 2400 mg/day [16], NAC was well tolerated and effective for treating a range of compulsive and addictive behaviors including obsessive compulsive disorder and drug use and craving (e.g., for methamphetamine and cannabis). A daily dose of up to 3600 mg/day of NAC has been shown to be safe and tolerable [16, 54]. Data collected from the trial will help improve our understanding of the potential utility of NAC to reduce compulsive eating. If it is found to be feasible, further larger scale studies to determine efficacy of the intervention will be undertaken.

Compulsive eating is a hallmark of some eating disorders including binge eating disorder [55, 56]. Approximately 3–5% of individuals with obesity in the general population and up to 30% of people seeking treatment for obesity have compulsive eating [57–59]. Compulsive eating is also the core feature of so-called “food addiction” that affects 5–15% of people in the community as measured by the Yale Food Addiction Scale (YFAS) [60–62]. Therefore, if proven efficacious, NAC may serve as an inexpensive, safe adjunct in the management of compulsive eating that could potentially benefit people with a broad range of conditions.

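### The stated 80% power belongs to a one-sided exact rule of at least 27/36 (75%), not to the 80% 'go' cut-off it is credited to, which true 80% retention meets only 57% of the time

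*Protocol article*

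**What the plan says.** All of this is in the Sample size estimation section of the protocol article. Retention means completing the retrospective questionnaires at week 12. The stated size is 36 participants. The hoped-for retention is 80% or better, and the comparator is given as "compared to a worst-case retention rate of 60% or less". The target power is 80% and the significance level 0.05. The calculation is said to be "based on the exact binomial test", although the same sentence also calls it a one-sample *t*-test. No side is given.

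The next sentence turns the two rates into a decision rule. It begins "The cut-off points of 60% and 80% set as the" and goes on to label them stop and go; these "criteria provides sufficient sample size and power for the assessment of the primary feasibility outcome".

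Neither 27/36 nor 75% appears anywhere in the article. The Outcome measures and Statistical analysis sections say only that retention will be calculated as a proportion. The Discussion makes later work depend on the outcome: "If it is found to be feasible, further larger scale studies to determine efficacy of the intervention will be undertaken".

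**The concern.** In a single-arm test of a proportion, the critical value lies between the null rate and the alternative rate. Here the alternative, 80%, is itself named as the go cut-off, and the power is credited to it. When the threshold equals the assumed true rate, the chance of passing is roughly that of a coin toss, so a stated power of 80% cannot describe that rule.

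Retention is a primary outcome and the only one used to size the study, so this is the one decision for which the article claims power. With 27 or 28 participants retained, the powered test rejects 60% while the written go criterion is not met. Unless the rule is settled in advance, someone will have to choose between the two after seeing the result.

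**Working it through.** **Inputs** (all from Sample size estimation): n = 36; null retention p0 = 0.60; alternative p1 = 0.80; alpha = 0.05, side not stated; target power 80%; exact binomial test; cut-offs 60% (stop) and 80% (go).

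**Step 1. Reproduce the 36.** For each n, find the smallest count r with P(X ≥ r | n, 0.60) ≤ 0.05. Power is then P(X ≥ r | n, 0.80).

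| n | r | r/n | alpha at 60% | power at 80% |
|---|---|---|---|---|
| 33 | 25 | 75.8% | 0.0444 | 0.79996 |
| 34 | 26 | 76.5% | 0.0341 | 0.773 |
| 35 | 27 | 77.1% | 0.0260 | 0.745 |
| 36 | 27 | 75.0% | 0.0449 | 0.832 |

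So 36 is the smallest n with one-sided exact power of at least 80%, and the plan's figure is reproduced. At n = 36 the next lower count, 26, has alpha 0.090, so 27 is the critical value.

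**Step 2. Check other readings of the test.**
- Two-sided exact test at 0.05, n = 36: the upper critical value is 28 (77.8%) and power is 0.716. Power first reaches 80% at n = 45 (upper tail 0.025) or n = 44 (minimum-likelihood method).
- Normal approximation: 33 one-sided (38 with continuity correction), 43 two-sided (47 with continuity correction).
- Arcsine: 32 one-sided, 41 two-sided.

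Of these, only the one-sided exact test gives 36.

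**Step 3. Apply the written go cut-off.** 0.80 × 36 = 28.8. Since 28/36 = 77.8% falls short, observed retention of at least 80% means at least 29/36 = 80.6%.

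| Rule at n = 36 | P(pass) at true 60% | P(pass) at true 80% |
|---|---|---|
| ≥27 (one-sided exact) | 0.045 | 0.832 |
| ≥28 (two-sided exact, upper tail) | 0.020 | 0.716 |
| ≥29 (observed ≥80%) | 0.007 | 0.566 |

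The chance of reaching 29 is 0.684 at true retention of 82% and 0.838 at 85%. It passes 80% at a true rate of about 84%.

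**Step 4. Where the misses fall.** 0.60 × 36 = 21.6, so observed retention of 60% or less means at most 21/36. At true 80%:
- P(X ≤ 21) = 0.0025 (stop)
- P(22 ≤ X ≤ 28) = 1 − 0.566 − 0.0025 = 0.43 (between the cut-offs)
- P(X ≥ 29) = 0.566 (go)

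**The case against.** The strongest reply is that 60% and 80% are only the null and alternative rates, meaning unacceptable and acceptable true retention. The wording *60% or less* points to a one-sided null, and on that reading 36 is right and the stated power is correct. The article nowhere says that go requires 29 of 36. This softens the point, because the error lies in how the rule is described and not in the sample size. It does not remove it: the text calls both figures cut-off points, labels them stop and go, and credits the power to them. A reader applying the protocol as written would use 80%.

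It is also fair to say that a go threshold stricter than the critical value is legitimate. What it needs is its own stated power.

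Three stronger inferences are not supported.
- A reader might conclude that a programme with 80% true retention would fail in more than four trials out of ten. It would miss go that often, but it would land at stop with probability of only 0.0025.
- A reader might infer that high retention alone yields go. The article does not say so: recruitment and adherence are also primary outcomes, and the Discussion refers to feasibility in general.
- A reader might count as defects the absence of cut-offs for adherence and recruitment, of an action between 60% and 80%, or of a confidence interval for retention. A journal article commonly leaves such detail to the full protocol or analysis plan, which are not shown here.

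**Conclusion.** The point holds as a mismatch between the stated power and the stated rule. The design behind n = 36 has a go boundary of 27/36 (75.0%), alpha 0.045 and power 83%. The rule as written, observed retention of at least 80%, needs 29/36 and has a 57% chance of go at true 80%, with a 0.7% chance at true 60%.

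Two assumptions matter. First, one-sidedness is inferred, because the text gives no side and only the one-sided exact test returns 36. If the test were two-sided, power would be 72% at 28/36, and the 80% cut-off would still lack the stated power. Second, the 57% applies if 80% is used as an observed threshold, which is how the text reads.

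Separately, the sizing sentence names two different procedures, a one-sample *t*-test and an exact binomial test; only the exact binomial test fits the figure of 36.

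This should be fixed but is not critical. The sample size stands, and no efficacy conclusion depends on the rule.

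**What to change.** In Sample size estimation, delete the reference to a one-sample *t*-test and state: one-sided exact binomial test, alpha 0.05, null hypothesis retention ≤60%. Then choose one of the following before retention results are read:

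1. Set go at 27 or more of 36 retained, with actual alpha 0.045 and power 83% at true 80%.
2. Keep go at observed retention of 80% or more (29 or more of 36), and restate the probability of go at true 80% as 57%, with 0.7% at true 60%.

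State plainly whether 80% is the assumed true rate or the observed threshold. The cost is a wording change with no added participants. The trade-off is between a lower go threshold under option 1 and a less favourable stated power under option 2.

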### Intervention

NAC will be administered orally at a daily dose of 2400 mg in capsule formulation for 12 weeks. It will be taken as two capsules of 600 mg twice daily, in the morning and evening with food. A systematic review of clinical trials of NAC found that at a dose of 2400 mg/day, NAC is well tolerated and effective for treating a range of compulsive and addictive behaviors including obsessive compulsive disorder and drug use and craving (e.g., for methamphetamine and cannabis) [16]. A daily dose of up to 3600 mg/day has been shown to be safe and tolerable [16]. The 10-item Medication Adherence Rating Scale [39], as well as pill count at the end of weeks 6 and 12, will be used to determine adherence with the study medication. Weekly interactions via phone calls or text messages between participants and the investigators will be conducted to maintain adherence to medication and study protocol.

### Recruitment and screening

Participants will be recruited via mailing lists and social media advertisements. Participants will express interest via an electronic form (REDCap) or by contacting the study researcher via email and will then be provided with the plain language statement and consent form. Prospective participants will complete an online questionnaire to screen eligibility. Participants who meet the requirements based on this initial screening will be invited to the study site at the Florey Institute of Neuroscience and Mental Health, Melbourne, Victoria, for further assessment to confirm eligibility.

### Assessment schedules

Prior to performing any study-specific procedure, written consent will be obtained for each participant. A study researcher will provide participants with the plain language statement and consent form. This document will describe the purpose of the study, the procedures to be followed, and the risks and benefits of participation. The study researcher will check that the participant comprehends the information provided and will answer any questions the participant has about the study. Participants will be given time to consider their involvement and an opportunity to discuss with relevant others. Participants will then be invited to provide written consent. Consent will be voluntary and free from coercion. When the eligibility of the participant has been confirmed, the participant will be assigned to intervention. The schedule of assessments is described in Table 1.

**Table 1 Tab1:** Schedule of assessments

TIME POINT	STUDY PERIOD				
	**Enrolment**	**Intervention period**			**Post-intervention**
	***Week-***_***1***_	***Week***_***1–4***_	***Week***_***5–8***_	***Week***_***9–12***_	***Week***_***13***_
**ENROLMENT**					
Eligibility screen	X				
Informed consent	X				
**INTERVENTIONS**					
NAC Intervention		X	X	X	
**ASSESSMENTS**					
Demographic characteristics	X				
Questionnaires*	X			X	
EMA survey#	X			X	
Monitoring of adverse effects		X	X	X	X
Medication adherence			X	X	

*Eating Loss of Control Scale, Palatable Eating Motives Scale, Food Craving Inventory, Reward-Based Eating Scale, Perceived Stress Scale, Emotional Eating Scale

^#^Last for a period of 7 days

### Safety monitoring

NAC has a good safety profile. Safety and monitoring will be overseen by the investigators (including medically trained personnel) who will regularly review adverse events. An independent medical monitor has been appointed to provide further safety oversight.

Adverse events and adverse reactions (non-serious and serious) will be captured from the time of administration of NAC until 7 days after the final dose and will be followed until resolution or stabilization. Assessment of any medically related changes in the participant’s well-being will be made at the end of weeks 3, 9, and 13 using open-ended questions via an online survey. In addition, in-person assessment will be done at the end of week 6 during the second visit to the study site. Each adverse event will be counted once for a given participant. If the same event is reported more than once, the event counted will be the event with the highest severity (coded mild, moderate, or severe). In the event that serious adverse effects occur, NAC medication will be suspended, and adequate medical care will be provided to the participant.

### Data management

Hard copy data will be stored in a locked cabinet in a secure workspace at the University of Melbourne, accessible to the research team only. Electronic data will be securely stored in the Florey Institute’s REDCap database system and secure network file servers, which are backed up regularly. The permissions granted to each user within the REDCap project will be controlled by the investigators. For EMA, data will be stored at the secure SEMA^3^ server housed at the University of Melbourne. Each participant is assigned a unique participant ID at enrolment. Data containing private or confidential information or data that can identify a participant will be accessible only by designated members of the research team. Following the completion of the study and data analysis, the data will be retained for the mandatory archive period (15 years).

### Outcome measures

The primary outcomes are participant retention rate, recruitment rate, and medication adherence. Retention rate will be calculated as the proportion of individuals who completed retrospective questionnaires at week 12. Recruitment rate will be assessed by calculating the number of recruited participants per month. Adherence to medication will be the percentage of doses taken, based on capsule count. The secondary outcome is change in Eating Loss of Control Scale score from baseline to week 12. The exploratory outcomes include the following:Adherence with EMA protocol (percentage of EMA surveys completed; percentage of participants who completed at least 80% of EMA surveys);Concordance between EMA and retrospective measures (internal consistency, convergent validity, and sensitivity to detect treatment outcome);Change of scores in the drivers of eating and eating behaviour from baseline to week 12:Emotional eating (Palatable Eating Motives Scale: Coping subscale and Emotional Eating Scale);Food craving (Food Craving Inventory);Preoccupation with food (Reward-based Eating Scale);Perceived stress (Perceived Stress Scale).

The outcomes will be assessed using both retrospective questionnaires (described below) and EMA.

#### Questionnaires

Sixvalidated questionnaires, including the Eating Loss of Control Scale [33], Palatable Eating Motives Scale: Coping Subscale [40], Food Craving Inventory [41], Reward-Based Eating Scale [42], Perceived Stress Scale [43], and Emotional Eating Scale [44], will be administered during baseline and post-NAC treatment assessment. Participants will be asked to complete these questionnaires electronically.

#### EMA measures

EMA survey will be delivered via an application installed on the participants’ mobile phone (SEMA^3^, University of Melbourne). Survey prompts will be sent three times per day (at semi-random times) over 7 days before and after NAC treatment. EMA questions will be modified from validated questionnaires including items from the Perceived Stress Scale (for stress level), Emotional Eating Scale (for mood/emotion), and Food Craving Inventory (for craving experience). Questions for loss of control eating were adapted from a previous study [45]. Mood/emotion, craving, perceived stress, loss of control eating, and preoccupation with food will be rated on a Likert scale consisting of a horizontal rating slider (1=*not at all* to 5=*extremely*), and exposure to specific food cues will require a yes/no answer.

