### Statistical analysis

All participants who received at least the first dose of study drug and provided at least 1 post baseline assessment will be included in the analysis. Data will be cleaned and checked for accuracy. Demographic characteristics will be summarized as proportions for categorical data and means and standard deviations for continuous data or medians as appropriate. For primary outcomes, retention rate will be calculated as the proportion of individuals who completed retrospective questionnaires at week 12; recruitment rate will be calculated as the total number of participants recruited divided by the total number of months that the trial recruited for. Secondary and exploratory outcomes will be reported as estimates of effects (95% confidence interval). Pearson or Spearman correlation will be used to analyze the concordance between EMA and retrospective measures (convergent validity), and reliability (internal consistency) will be examined with Cronbach’s alpha. Compliance rate will be estimated from the average number of EMA surveys completed out of all administered surveys.

Adverse events will be reported as the number and percentage of participants reporting adverse events. Other information about each adverse event including start date, stop date, severity, relationship, expectedness, outcome, and duration, including adverse events leading to premature discontinuation from the trial intervention and serious treatment-emergent adverse events, will also be collected.

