## Discussion

This study will test the feasibility of delivering a 12-week NAC intervention and assessing responses using EMA for 7 days before and after the intervention in people with loss of control eating. Treatment outcomes related to eating behaviour are commonly evaluated using retrospective questionnaires. The disadvantage of this approach is the potential influence of recall bias. EMA is typically administered via a smartphone-based application with multiple sampling (i.e., several times per day over days to weeks) and provides close to real-time data. This may be advantageous in detecting associations between factors involved in eating behavior, especially those with a dynamic nature such as stress and mood. In the field of eating disorders, there has been a substantial growth in the number of studies employing EMA in the last few years. These studies have focused on understanding the theoretical model of eating disorders, examining the antecedents/predictors and consequences of eating behaviors, and understanding the relationship between variables implicated in eating disorder [46]. Notably, the majority of studies using EMA are observational and have not employed this assessment in the context of detecting treatment outcomes. EMA has been used to study treatment outcomes in some psychiatric disorders such as substance use disorder, anxiety disorder, depression, attention-deficit hyperactivity disorder (ADHD), and psychotic disorders [47]. During antidepressant treatment in patients with major depressive disorder, EMA was able to detect subtle early changes in affect that were predictive of later response and remission [48]. Another advantage of using EMA during treatment is its sensitivity to detect context-specific treatment effects. An EMA study in smokers with ADHD showed that ADHD medication improved concentration specifically during stress and smoking abstinence [49]. Moreover, EMA is more sensitive than retrospective questionnaires in capturing changes in health-related quality of life following cardiac interventions [50]. This study will be among the first to employ EMA to measure the effects of an intervention on loss of control eating. However, the reliance of EMA on repeated daily measurement for long periods may be burdensome for participants and affect adherence rate. Thus, comparing the result of EMA measures with retrospective questionnaires will allow researchers to choose between the approaches that best fit with the study objectives when conducting future studies. Studies on feasibility of EMA commonly look at participants’ acceptability of the assessment, response rate to survey prompts, retention rate, initial validity and reliability of EMA data, and identification of technical issues which may arise during the study [51–53]. Our pilot study will collect this information as a basis for designing a future RCT.

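### The EMA items listed for emotional eating rate mood, so a correlation of EMA mood with the emotional-eating scales cannot be read as convergent validity, whether high or low

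*Protocol article*

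**What the plan says.** In the protocol article, Outcome measures lists four exploratory outcomes for drivers of eating and eating behaviour. One is "Emotional eating (Palatable Eating Motives Scale: Coping subscale and Emotional Eating Scale"). The section ends: "The outcomes will be assessed using both retrospective questionnaires (described below) and EMA". It also lists "Concordance between EMA and retrospective measures (internal consistency, convergent validity, and sensitivity to detect treatment outcome") as an exploratory outcome.

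EMA measures says where the EMA questions come from. What EMA takes from this source is given as "Emotional Eating Scale (for mood/emotion"). The rated constructs follow: "Mood/emotion, craving, perceived stress, loss of control eating, and preoccupation with food will be rated on a Likert scale", on a five-point slider whose anchors grade intensity. Exposure to food cues is answered yes or no.

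Statistical analysis gives the method for comparing the two modes: "Pearson or Spearman correlation will be used to analyze the concordance between EMA and retrospective measures (convergent validity"). Cronbach's alpha is added for internal consistency.

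The Discussion gives as a possible advantage of EMA that it helps in "detecting associations between factors involved in eating behavior, especially those with a dynamic nature such as stress and mood".

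**The concern.** The article's Background describes this kind of eating as triggered by feelings such as anger, boredom or stress. Emotional eating is therefore a link between feeling and eating, not a level of feeling. Someone whose mood is often low but who does not eat in response would score high on EMA mood and low on the questionnaire. Someone usually in good mood who eats whenever upset would show the reverse.

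If EMA mood stands in for emotional eating, the concordance coefficient compares two constructs. A fall in mean negative mood after treatment could also be taken for a fall in emotional eating, which would affect the comparison of the two modes' sensitivity to treatment. Comparing EMA with questionnaires is a stated aim, and the Abstract says the study will determine which approach suits the research. For this construct, the planned coefficient could not inform that choice.

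**Working it through.** **Step 1. Match each outcome to its EMA rating** (from Outcome measures, Questionnaires and EMA measures).

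| Outcome | Questionnaire | EMA rating of the same construct |
|---|---|---|
| Loss of control eating | Eating Loss of Control Scale | yes |
| Food craving | Food Craving Inventory | yes |
| Preoccupation with food | Reward-Based Eating Scale | yes |
| Perceived stress | Perceived Stress Scale | yes |
| Emotional eating | Emotional Eating Scale; Coping subscale | none listed; mood/emotion only |

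The mismatch also runs the other way: none of the six questionnaires is described as a mood measure, so EMA mood has no like-for-like retrospective partner.

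**Step 2. How many data there are.** The article gives 3 prompts a day for 7 days, before and after treatment. 3 × 7 = 21 per block; × 2 = 42 per participant; × 36 = 1,512 with no dropout, or about 1,210 at 80% completion. At the 80% retention used for the sample size, 0.80 × 36 = 28.8, so about 29 participants have both assessments.

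**Step 3. What the coefficient would measure.** The plan states no figure on this point, so this is an illustration on assumed values. Let emotional eating be each person's slope of eating on mood, with SD 0.3. Let mood have between-person SD 0.7 and within-person SD 1, residual SD be 1, and questionnaire reliability be 0.8. Let ρ be the correlation between a person's usual mood level and their slope.

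- Mean mood against the questionnaire: r ≈ ρ × √0.8 × √[0.49 / (0.49 + 1/21)] = ρ × 0.894 × 0.955 = 0.854ρ. For ρ = 0, 0.3 and 0.5 this gives 0, 0.26 and 0.43. Simulation gave 0.00, 0.25 and 0.43.
- Within-person slope against the questionnaire: the error variance of a slope from 21 prompts is about 1/18 = 0.056, so r ≈ √0.8 × √[0.09 / (0.09 + 0.056)] ≈ 0.70, whatever ρ is. Simulation gave 0.70 in all three cases, and about 0.66 to 0.67 with 17 of 21 prompts answered.

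The first coefficient reflects ρ, which is a fact about people and not about how well EMA works. The second is favourable by construction, because the illustration defines emotional eating as the slope. It shows that a slope from 21 prompts can carry information; it does not validate the slope as a measure.

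**Step 4. Precision.** The 95% interval is tanh[atanh(r) ± 1.96/√(n − 3)].

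| r | n = 36 | n = 29 |
|---|---|---|
| 0.3 | −0.03 to 0.57 | −0.07 to 0.60 |
| 0.7 | 0.48 to 0.84 | 0.45 to 0.85 |

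**The case against.** The strongest reply is that the faulty pairing is not written down. Statistical analysis names no pairs and no EMA scoring rule, and both are commonly left to a fuller document. The item wording is not shown either, and a modified Emotional Eating Scale item could keep an urge-to-eat stem. The sentence that outcomes are assessed both ways is loose, since it follows a list that includes recruitment rate and capsule counts. The Discussion's remark on associations is background and commits the study to no analysis.

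Much of this stands. It rules out three stronger readings that a reader might infer:

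- **That the correlation will be low and EMA wrongly judged discordant.** The assumed cases run from 0 to 0.43, and the article states no concordance threshold.
- **That EMA cannot yield any measure of emotional eating.** Mood and loss of control are both rated at the prompts, and correlating a slope with a questionnaire is still a correlation of an EMA measure with a retrospective one.
- **That leaving out a within-person model is itself an error.** A condensed article may leave such a model to the full plan.

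It is also fair that a slope of loss of control or craving on mood is not emotional eating itself, since the article treats these as separate outcomes. Hence the slope can only be a proxy.

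What does not fall away is that the three stated elements do not fit together: an outcome said to have an EMA version, EMA items described as mood ratings, and a mode-against-mode correlation. If the items do keep an urge-to-eat stem, the description in EMA measures is wrong and still needs correcting.

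**Conclusion.** The point holds in a limited form. As described, EMA has no item for eating in response to emotion or to cope, so a correlation of EMA mood level with the Emotional Eating Scale or the Coping subscale cannot be interpreted as convergent validity at any value. Equally, a change in mean EMA mood is not a change in emotional eating.

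This concerns one of four exploratory driver outcomes, covering two of the six questionnaires. Recruitment, retention, medication adherence and the secondary outcome are unaffected. The conclusion rests on taking the article's mood/emotion description and intensity anchors at face value. The correlations in the illustration rest on assumed variances and show only that the coefficient is uninformative, not what it will be.

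**What to change.** - Report mean EMA mood as mood only. Do not count its correlation with the Emotional Eating Scale or the Coping subscale as evidence for or against EMA concordance.
- Define an exploratory EMA index of emotional eating and label it a proxy: the within-person association between person-mean-centred mood and the loss-of-control (or craving) rating, from a mixed model with a random slope. Choose the rating and the timing (same or next prompt) in advance.
- Relate this index to the two scales with a 95% interval, and estimate its change with a mood-by-period term.
- If the actual EMA items ask about the urge to eat, correct the mood/emotion label in EMA measures instead; the proxy is then not needed for the Emotional Eating Scale.

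Simpler alternatives would also remove the mismatch: add an EMA item on eating in response to emotion, or take emotional eating out of the outcomes said to be assessed by EMA.

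The main fix costs some wording and one model on data already planned. Its downside is imprecision: slopes come from at most 21 prompts per block in about 29 to 36 participants, so the interval matters more than the point estimate.
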